## Abstract

**Background:**

Atrial fibrillation (AF) is a common condition leading to an increased risk of death and complications such as stroke. Even though direct oral anticoagulants (DOACs) can reduce the risk of ICH, the rate of DOAC use remains low in many Asian countries because of cost concerns.

**Objectives:**

The purpose of this protocol paper of the COOL-AF (COhort of antithrOmbotic use and cLinical outcomes in patients with Atrial Fibrillation) Phase 2 registry is to determine the rate of clinical outcome, changes in antithrombotic patterns, and their impact on clinical outcomes, and to develop a prediction model for clinical outcomes.

**Methods:**

The COOL-AF Phase 2 study is a prospective observational multicenter study of patients with known or newly diagnosed nonvalvular AF in Thailand. The aim is to achieve a sample size of 3,667 patients from 33 centers. Patients will be followed up every 6 months for up to 3 years. Data collection on and doses of oral anticoagulants (warfarin, dabigatran, rivaroxaban, apixaban, and edoxaban) and antiplatelets are collected. The study outcomes include death, ischemic stroke/systemic embolism, major bleeding, myocardial infarction, heart failure, and quality of life. All events will be adjudicated.

**Results:**

Enrollment started in June 2024. The results of the COOL-AF phase 2 registry will be reported when enrollment is complete and one year of follow-up data is available.

**Conclusions:**

The COOL-AF Phase 2 trial will provide valuable information about the real-world practice of AF management and outcomes in Asia, which should be able to improve AF outcomes in the future. (COhort of antithrOmbotic Use and cLinical Outcomes in Patients With Atrial Fibrillation [COOL-AF] Phase 2; NCT06396299)

Atrial fibrillation (AF) is a common heart rhythm disorder that tends to increase in prevalence with advancing age.^1^ Besides its high global prevalence, AF also poses a significant health and financial burden.^2^ Patients with AF have approximately a 5% annual risk of developing ischemic stroke, which is about 5 times higher than that of individuals without AF.^3^^,^^4^

Most AF patients should receive stroke prevention with oral anticoagulants (OACs).^5^^,^^6^ Warfarin remains the primary OAC used in many Asian countries^5^^,^^7^ despite its disadvantages, including an increased risk of intracranial hemorrhage (ICH), a narrow therapeutic window, interacting with a wide range of foods and drugs, and a slow onset and offset of action.^8^ It is essential to monitor the international normalized ratio (INR) through blood tests to assess the medication's effectiveness.^9^ The dosage of the medication varies and is challenging to predict for each patient. Genetic factors that influence drug levels, and preliminary data indicate that the Asian population differs from Western countries,^10^ with a higher risk of ICH.^11^

Currently, there is a global shift in the guidelines for anticoagulant therapy, including in Thailand, where the use of direct oral anticoagulants (DOACs) for preventing ischemic stroke has become increasingly widespread.^12^, ^13^, ^14^ This trend is caused by their convenience of use, the lack of need for blood monitoring, and a reduced risk of bleeding, especially ICH, compared with warfarin. However, there are still limitations in accessing these medications in many low- or middle-income countries.^15^ Currently, DOACs are not included in the Thai National List of Essential Drugs because they are considered expensive drugs. A cost-utility analysis study in Thailand showed that all DOACs are not cost-effective at the current willingness to pay level in Thailand.^16^ It is recommended that DOACs be included in the World Health Organization Essential Medicines List.^17^ This is related to the low willingness to pay level in Thailand per quality-adjusted life year.^18^ It is uncertain whether the results from clinical trials can be applied in a real-world setting. The COOL-AF (COhort of antithrOmbotic use and cLinical outcomes in patients with Atrial Fibrillation) Phase 2 trial was initiated and funded by the Health Systems Research Institute and the Heart Association of Thailand under Royal Patronage. We intend to retain the acronym of the COOL-AF registry but with a different title because the original COOL-AF was planned to determine the optimal INR levels for those on warfarin. The COOL-AF Phase 2 aims to determine the clinical outcome of AF patients and to investigate contemporary antithrombotic treatment patterns for stroke prevention in patients with AF in Thailand and their impact on clinical outcomes. The primary objectives were as follows: 1) to determine the rate of clinical outcomes (death, SSE, and major bleeding); 2) to develop the prediction model for clinical outcomes; and 3) to determine the antithrombotic pattern and the effect on clinical outcomes. The secondary objectives were as follows: 1) to study the predictors for clinical outcomes; 2) to determine the effect of DOAC dosing on clinical outcomes, and to determine the effect of TTR on clinical outcomes in patients with warfarin; and 3) to validate model from COOL-AF phase 1, and to study economic analysis (Table 1).

**Table 1 tbl1:** The Study Objectives

Primary objectives
To study the patterns of antithrombotic medication usage in patients with atrial fibrillation
To investigate the clinical outcome rates (including all-cause mortality, ischemic stroke/transient ischemic attack/systemic embolism, intracranial hemorrhage, and major bleeding) in atrial fibrillation patients
To develop predictive model for clinical outcomes
Secondary objectives
To investigate the factors predicting clinical outcomes in patients with atrial fibrillation;
To study the clinical outcome rates (including all-cause mortality, ischemic stroke/transient ischemic attack/systemic embolism, intracranial hemorrhage, and major bleeding) in atrial fibrillation patients stratified by different types of antithrombotic medications, including warfarin, stratified by TTR, the 4 types of DOACs, stratified by dosage, and antiplatelet agents;
To validate data from COOL-AF Phase 1, such as the COOL-AF predictive models for all-cause mortality, ischemic stroke/systemic embolism, and major bleeding; and
To conduct an economic analysis of the complications related to ischemic stroke and the cost-effectiveness of stroke prevention and treatment in atrial fibrillation patients.

COOL-AF = COhort of antithrOmbotic use and cLinical outcomes in patients with Atrial Fibrillation; DOAC = direct oral anticoagulant; TTR = time in therapeutic range.

## Methods

### Study design

COOL-AF Phase 2 is a prospective multicenter observational study for men and women older than 18 years with known or newly diagnosed AF documented by standard 12-lead ECG or Holter monitoring. We expect to enroll 3,667 patients from 33 centers distributed across different regions of Thailand (Figure 1).

**Figure 1 fig1:**
[figure not shown]
Study Sites for COOL-AF Phase 1 and 2 Registries This figure shows the locations of hospitals participating in the COOL-AF (COhort of antithrOmbotic use and cLinical outcomes in patients with Atrial Fibrillation) registry. (A) 27 hospitals involved in Phase 1, (B) 33 hospitals participating in Phase 2. The expansion in Phase 2 provides wider coverage across Thailand, allowing for better data collection on antithrombotic use and clinical outcomes in patients with atrial fibrillation.

The study was approved by the Central Research Ethics Committee (CREC) (COA-CREC103/2023). The methodology of this study was in accordance with the principles set forth in the Declaration of Helsinki and the International Conference on Harmonization for Good Clinical Practice Guidelines. All patients will provide written informed consent before participation. Participants have the right to withdraw their consent at any time after the enrollment.

### Study population

We studied patients with nonvalvular AF. Inclusion and exclusion criteria are shown in Table 2. The decision for enrollment depends on the judgment of the physician after consideration of the study criteria. To avoid bias, investigators were instructed to ensure consecutive patient enrollment. All required data will be recorded in the electronic web-based system.

**Table 2 tbl2:** Inclusion and Exclusion Criteria of the Study Population

Inclusion Criteria	Exclusion Criteria
1. Participants age 18 y and older with atrial fibrillation diagnosed based on a 12-lead ECG or ECG tracing from ambulatory ECG monitoring 2. Participants must be willing to provide written informed consent to participate in the study.	1. Patients who have experienced an ischemic stroke within the past 3 mo before enrollment. 2. Patients with a platelet count of <100,000/mm^3^ or who have myeloproliferative disorders (essential thrombocythemia, chronic myeloid leukemia, polycythemia vera, agnogenic myeloid metaplasia), hyperviscosity syndrome, chronic disseminated intravascular coagulation, or antiphospholipid syndrome. 3. Patients with a mechanical prosthetic heart valve. 4. Patients with rheumatic mitral stenosis. 5. Patients participating in research projects with concealed treatments. 6. Patients expected to have a life expectancy of <3 y because of other diseases, such as cancer or acquired immune deficiency syndrome, as determined from medical records. 7. Pregnant patients. 8. Patients unable to follow the treatment plan. 9. Patients who have been hospitalized or discharged from the hospital within the past 1 mo.

ECG = electrocardiogram.

Patients will be identified from various sources such as the anticoagulation clinic, cardiology clinic, internal medicine clinic, geriatric clinic, and emergency department.

### Study protocol

After the consent process, investigators will record the required data from medical records and patient interviews. Patient data will be recorded in the web-based system that was created to be user-friendly for data entry. After the data entry is completed, the site investigators will submit the data.

Follow-up visit data will be recorded at 6, 12, 18, 24, 30, and 36 months after enrollment. The follow-up data will be recorded in a similar manner. The window period of data recording will be 1 month. Email reminders will be sent out to site investigators every 2 weeks to remind them of any overdue of the data entry or the incomplete record. The timeline of the study is shown in Figure 2.

**Figure 2 fig2:**
[figure not shown]
Enrollment and Follow-Up Timeline for COOL-AF Phase 2 This figure shows the timeline for the COOL-AF (COhort of antithrOmbotic use and cLinical outcomes in patients with Atrial Fibrillation) Phase 2 registry, starting with the first patient enrollment in June 2024. The last patient is expected in 2026. Follow-up assessments will take place at 6, 12, 18, 24, 30, and 36 months for each patient. The key clinical outcomes are tracked throughout the study. These outcomes include all-cause death, ischemic stroke, systemic embolism, major bleeding, myocardial infarction, heart failure, and quality of life.

### Data collection

The following data were collected at the baseline visit:•Demographics (age, sex, weight, height)•Type of AF (new, paroxysmal, persistent, permanent)•Symptoms of AF (dyspnea, palpitations, dizziness, chest pain, syncope, fatigue, and the European Heart Rhythm Association score)•Duration of AF•Method of AF diagnosis•Medical history (history of stroke/transient ischemic attack [TIA], carotid surgery/stenting, percutaneous coronary intervention, coronary artery bypass surgery, myocardial infarction, peripheral arterial disease, bleeding history, heart failure)•Cardiovascular risk factors (hypertension, type 2 diabetes (T2D), smoking, dyslipidemia]•AF management (rate control, rhythm control, cardioversion, ablation)•Anticoagulant/antiplatelet therapy•Vital signs (blood pressure, heart rate)•INR values and dates•Other laboratory values•Cardiac imaging results•Components of the CHA_2_DS_2-_VASc score•Components of the HAS-BLED score•Components of the SAMe-TT2R2 score•EQ-5D-5L

Because antithrombotic pattern is one of the main interests of this registry, the data collection on the antithrombotic agents included the types and doses of OAC and antiplatelets. Anticoagulants are vitamin K antagonist (warfarin), and DOACs (dabigatran, rivaroxaban, apixaban, and edoxaban). Doses of DOACs are recorded as follows: dabigatran 110 and 150 mg twice daily, rivaroxaban 10, 15, or 20 mg once daily, apixaban 2.5 or 5 mg bid, and edoxaban 15, 30, or 60 mg od. Antiplatelets are aspirin and P2Y12 inhibitors (clopidogrel, prasugrel, and ticagrelor). Doses of aspirin are recorded. Combination of OAC and antiplatelet is also recorded. Data collection at the follow-up visit was similar to that at the baseline visit with the addition of clinical events and data related to that event. The source document of the clinical outcomes was required to be uploaded into the web system.

Schedule of study procedures at baseline and follow-up is shown in Table 3. Summary of study protocol and design of the COOL-AF Phase 2 study is shown in the Central Illustration.

**Table 3 tbl3:** Schedule of Study Procedures

	Initial Visit	Data Collection Interval					
		6 mo	12 mo	18 mo	24 mo	30 mo	36 mo
Assessments (prescreen)							
Informed consent	√						
Inclusion/exclusion criteria	√						
Demographics	√						
Diagnosis	√						
Symptoms of AF	√	√	√	√	√	√	√
Cardiovascular history	√						
Additional medical history	√						
Bleeding history and risk factors for bleeding							
Vital signs	√	√	√	√	√	√	√
Investigations							
Laboratory INR values	√	√	√	√	√	√	√
Other laboratory findings	√	√	√	√	√	√	√
Cardiac imaging	√	√	√	√	√	√	√
AF treatment							
Nonmedication treatment	√	√	√	√	√	√	√
Rate and rhythm control medication	√	√	√	√	√	√	√
Antithrombotic therapies	√	√	√	√	√	√	√
Other medications	√	√	√	√	√	√	√
Components of CHA_2_DS_2_-VASc score	√	√	√	√	√	√	√
Components of HAS-BLED score	√	√	√	√	√	√	√
Components of SAMe-TT2R2 score	√	√	√	√	√	√	√
Outcomes		√	√	√	√	√	√
Quality of life (QOL) questionnaires							
EQ5D-5L	√				√		√

AF = atrial fibrillation, INR = international normalized ratio.

**Central Illustration undfig2:**
[figure not shown]
Design of the COOL-AF Phase 2 Registry and Clinical Outcomes The design of the COOL-AF (COhort of antithrOmbotic use and cLinical outcomes in patients with Atrial Fibrillation) Phase 2 registry, a prospective observational study involving 3,667 atrial fibrillation (AF) patients from 33 hospitals in Thailand. The timeline shows patient enrollment starting in June 2024, with follow-up assessments every 6 months. The study tracks key clinical outcomes, including all-cause death, ischemic stroke, systemic embolism, major bleeding, myocardial infarction, heart failure, and quality of life. The primary goal is to identify gaps in AF care and analyze real-world patterns of antithrombotic use to improve patient outcomes.

### Outcomes

Details of clinical outcomes are shown in Table 4. The definitions of main clinical outcomes are as follows:•Ischemic stroke/TIA: acute onset of focal neurological deficit that persists more than 24 hours for ischemic stroke, and <24 hours for TIA. Imaging data from computed tomography brain scans or cardiac magnetic resonance are required to be uploaded into the web-based system.•Major bleeding: International Society of Thrombosis and Haemostasis criteria.^19^ It is defined as intracranial hemorrhage, intraspinal hemorrhage, intraocular/retinal hemorrhage, intra-articular hemorrhage, or intramuscular hemorrhage with compartment syndrome, or any bleeding that leads to a reduction in hemoglobin of ≥2 mg/dL from baseline. Minor bleeding is defined as any bleeding that did not fulfill any of the major bleeding criteria.•HF event: a hospital admission or a presentation of the patient for an urgent, unscheduled clinic, office or emergency department visit, with a primary diagnosis of HF. The clinical presentation may be new or worsening of HF symptoms, and there must be objective evidence of new or worsening HF, along with the initiation or intensification of treatment specifically for HF.^20^•Myocardial infarction: Clinical syndrome characterized by evidence of myocardial necrosis in patients with a clinical setting consistent with acute myocardial ischemia.^21^

**Table 4 tbl4:** Main Outcome Measures

Outcome Measures	Types
Clinical events	Ischemic stroke/TIA Systemic embolization Heart failure Myocardial infarction Death Cause of death (cardiovascular, noncardiovascular including details)
Bleeding events	
Severity	Major bleeding (ICH, non-ICH) Minor bleeding
Location	Intracranial Intraspinal Intraocular/retinal Retroperitoneal Intra-articular Pericardial Intramuscular with compartment syndrome Intramuscular without compartment syndrome Epistaxis Upper GI Lower GI Oral cavity Hemoptysis Prolonged menstrual Macroscopic hematuria Rectal Skin Subconjunctival
Outcome	Fatal Nonfatal
Health care used for bleeding event	Hospitalization (length of stay and cost) Transfusion
OAC persistence	Rate of discontinuation Duration of time on therapy Reasons for discontinuation
Hospital visits	Number of hospital visits related to AF
Patients treated with vitamin K antagonists	Number, date of INR monitoring Time in the therapeutic range Warfarin dose Type of test (central laboratory or POCT) Setting (OPD or IPD) Warfarin interruption and use of bridging

ICH = intracranial hemorrhage; IPD = inpatient department; OAC = oral anticoagulant; OPD = outpatient department; POCT = point of care test; TIA = transient ischemic attack.

The source documents are required to be uploaded into the web-based system for the verification of clinical outcomes. All source documents, including imaging for those who had a stroke or TIA, are sent to the adjudication committee for confirmation of the clinical outcome.

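### The only stated definition of major bleeding sets the hemoglobin fall in mg/dL, a threshold too small to measure, and has no criterion for fatal, retroperitoneal, pericardial or transfused bleeding

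*Protocol article*

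**What the plan says.** The Outcomes section of the protocol article opens the definition by naming a source: "Major bleeding: International Society of Thrombosis and Haemostasis criteria". It then states a rule of its own, beginning with five sites: "It is defined as intracranial hemorrhage, intraspinal hemorrhage, intraocular/retinal hemorrhage, intra-articular hemorrhage, or intramuscular hemorrhage with compartment syndrome". For bleeds elsewhere, the alternative route to a major classification is a hemoglobin criterion: "any bleeding that leads to a reduction in hemoglobin of ≥2 mg/dL from baseline". The remainder is handled by exclusion: "Minor bleeding is defined as any bleeding that did not fulfill any of the major bleeding criteria".

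Table 4 in the same section lists what is collected for each bleed. The locations include "Intracranial Intraspinal Intraocular/retinal Retroperitoneal Intra-articular Pericardial Intramuscular with compartment syndrome", followed by sites such as epistaxis, skin and subconjunctival. Outcome is recorded as "Fatal Nonfatal", and health care used as "Hospitalization (length of stay and cost) Transfusion".

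No other part of the article restates the hemoglobin criterion, changes its unit or adds a criterion. The text after Table 4 sends source documents to an adjudication committee, but gives no separate rule for the committee to apply.

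**The concern.** There are two defects in one operative definition.

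- **Unit.** Hemoglobin falls of clinical interest are on the scale of g/dL. A threshold in mg/dL is met by any fall that a laboratory can report, so the criterion no longer separates major from minor bleeding.
- **Incomplete list.** Four features that the registry records (fatal outcome, retroperitoneal site, pericardial site, transfusion) have no place in the written rule. Because minor bleeding is the complement of major, anything the rule omits becomes minor by default.

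The outcome carries much of the plan. The major bleeding rate is part of the first primary objective. Under Sample size calculation, major bleeding is one of the three outcomes for which a prediction model is sized. It is an outcome in the comparison of antithrombotic patterns, and Table 1 lists a Phase 1 major bleeding model for validation. Each of these uses needs one event definition that every site and adjudicator applies in the same way.

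**Working it through.** **1. The plan's own sample size, to see whether it depends on this definition.** Inputs from Sample size calculation: 10 events per candidate variable, about 10 candidate variables, 3,334 patients (the highest requirement, for SSE), and 10% incomplete or lost follow-up.

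- Events needed: 10 × 10 = 100.
- Implied SSE proportion: 100 / 3,334 = 3.0%.
- With the allowance: 3,334 × 1.10 = 3,667.4, which agrees with the stated 3,667.

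SSE sets the number, so correcting the bleeding definition does not change it.

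**2. The unit.** Since 1 g = 1,000 mg, 2 mg/dL = 2 / 1,000 = 0.002 g/dL. Against 2 g/dL the ratio is 2 / 0.002 = 1,000.

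The article gives no hemoglobin values, so the following inputs are assumptions.

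| Assumption | 2 mg/dL as printed | 2 g/dL |
|---|---|---|
| Hemoglobin 8 g/dL | 0.002 / 8 = 0.025% | 2 / 8 = 25% |
| Hemoglobin 16 g/dL | 0.002 / 16 = 0.0125% | 2 / 16 = 12.5% |
| Reporting step 0.1 g/dL | 0.1 / 0.002 = 50, so one step is 50 times the threshold | 2 / 0.1 = 20 steps |

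The conclusion does not depend on the exact reporting step. With any step coarser than 0.002 g/dL, the smallest reportable fall already meets the printed threshold.

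**3. The written rule set beside Table 4.**

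| Feature | In the written definition | Recorded in Table 4 |
|---|---|---|
| Intracranial, intraspinal, intraocular/retinal, intra-articular, intramuscular with compartment syndrome | yes | yes, location |
| Retroperitoneal | no | yes, location |
| Pericardial | no | yes, location |
| Fatal | no | yes, outcome |
| Transfusion | no | yes, health care used |

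**4. How a bleed outside the five named sites is classed under each reading of the unit.**

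| Hemoglobin fall attributed to the bleed | As printed | Read as g/dL |
|---|---|---|
| None recorded (for example, no second sample, or one taken only after transfusion) | minor, even if fatal, retroperitoneal, pericardial or transfused | minor, likewise |
| Recorded, below 2 g/dL | major, even if trivial | minor, even if fatal, retroperitoneal, pericardial or transfused |
| 2 g/dL or more | major | major |

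The printed unit pushes trivial bleeds up, but it also brings in most of the omitted bleeds through the hemoglobin criterion. Reading g/dL removes the first error and widens the second. Neither reading gives a definition consistent with the features the registry collects.

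**5. The reference value.** The criterion counts the fall from baseline without saying which baseline. Data collection uses that word for the enrollment visit, while Table 3 schedules laboratory findings at every 6-month visit. The reference could be the enrollment value or the latest value before the bleed.

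**The case against.** The case on the other side has five parts.

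- **The unit is a misprint.** Probably so, since a threshold below what can be measured is unlikely to be intended. But it stands in the sentence that defines the outcome and is corrected nowhere. Reading it silently as g/dL leaves the incomplete list in place and makes it matter more.
- **The cited criteria govern, and a committee adjudicates.** This may limit the harm in practice. The article does not say so: after the citation it introduces its own list as the definition, and it shows no other rule for adjudicators.
- **A journal article condenses.** It may omit detail. Here it states a definition, and the unit in that definition is wrong. Whether the eCRF or the adjudication instructions carry the same unit is unknown.
- **Table 4 covers all bleeding.** Correct. Listing a site or a transfusion there does not make it a criterion for major bleeding, so the table does not contradict the definition. It shows that the information is available and that the rule leaves it unused.
- **The fall must be caused by the bleed.** This stands, and it limits the upward error. One might infer that about half of nuisance bleeds would count as major. With no true fall, an assumed SD of 0.2 to 0.5 g/dL between readings and a 0.1 g/dL step, chance alone gives 40% to 46%. That calculation ignores the causal wording, as does the idea that slow anemia drift would count, so neither is supported.

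Three other stronger readings also fail. The two directions of error do not both act at full strength, as step 4 of the working shows. The reference value is ambiguous, not shown to be up to three years old. Loss of comparability with Phase 1 or with the cited criteria cannot be asserted, because neither definition is shown.

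**Conclusion.** The point holds. The only stated definition of an outcome in the first primary objective has a threshold 1,000 times below 2 g/dL, and a list that does not provide for fatal, retroperitoneal, pericardial or transfused bleeding. Read literally, any recorded fall attributed to a bleed makes it major. A bleed outside the five sites with one of those four features but no recorded fall is minor. If the unit is taken as g/dL, the first consequence disappears and the second reaches further, to falls below 2 g/dL.

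The unit conversion and the comparison with Table 4 need no outside source. That the printed threshold is unmeasurable assumes only that hemoglobin is reported in steps coarser than 0.002 g/dL. The number of misclassified events cannot be computed from the document, and the effect on rates, models or treatment comparisons is likewise unquantified. The sample size stands.

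**What to change.** 1. Correct the unit of the hemoglobin criterion to g/dL.
2. State that the fall is measured from the last hemoglobin value before the bleed.
3. Either state that the cited ISTH criteria govern and the list is only illustrative, or complete the list so that it deals explicitly with fatal bleeding, retroperitoneal and pericardial sites, and transfusion.
4. Put the same text in the eCRF help and the adjudication instructions.
5. Recheck any events already classified under the printed wording.

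The first four steps are wording changes. Table 4 already captures fatality, location and transfusion, so no new outcome field is needed for those items. The small downside is the recheck. Enrollment began in June 2024, so any delay may add to the events that need it.

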### Sample size calculation

The sample size calculation for the predictive model development was based on the 10 events per variable concept, which suggested that we need at least 10 events per candidate variable.^30^ The results from COOL-AF phase 1 indicated that the number of candidate variables for death, SSE, and major bleeding is approximately 10. Using the rate of death, SSE, and major bleeding from COOL-AF phase 1,^3^ the number of patients needed for predictive model development was highest at 3,334 for SSE. If the rate of incomplete or loss follow-up is 10%, the sample size needed was 3,667. This sample size also covers the sample size needed to determine the rate of clinical outcomes (death, SSE, and major bleeding).

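### The hemoglobin criterion for major bleeding is written in mg/dL, one thousandth of the same figure in g/dL and too small for a laboratory to resolve

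*Protocol article*

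**What the plan says.** The Outcomes section of the protocol article opens the definition with "Major bleeding: International Society of Thrombosis and Haemostasis criteria" and a citation. It then gives its own wording: bleeding at a list of critical sites (intracranial, intraspinal and others) or "any bleeding that leads to a reduction in hemoglobin of ≥2 mg/dL from baseline". The next sentence makes the other category a remainder: "Minor bleeding is defined as any bleeding that did not fulfill any of the major bleeding criteria".

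This is the only numeric criterion in the definition. Table 4 lists major and minor bleeding, and bleeding locations such as epistaxis, oral cavity, skin and subconjunctival, without any hemoglobin threshold. The text after Table 4 says that source documents "are sent to the adjudication committee for confirmation of the clinical outcome", and Study strengths repeats that each outcome is confirmed. Neither place states a threshold.

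Major bleeding is central to the study. The first primary objective in the introduction is "to determine the rate of clinical outcomes (death, SSE, and major bleeding"), and Table 1 names it again among the primary and secondary objectives. Sample size calculation treats it as one of three outcomes with about 10 candidate variables each.

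**The concern.** Hemoglobin concentrations are ordinarily expressed in g/dL. A cut-off of a few mg/dL lies below what a laboratory report can show, so it cannot separate large bleeds from small ones. In effect the criterion becomes whether any fall at all was recorded and put down to the bleed.

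The major-bleeding event is the input to several planned analyses: the incidence rate per 100 person-years, the Cox models of predictors and of antithrombotic pattern, the prediction model, and the validation of the Phase 1 major-bleeding model. If the written unit were applied, small bleeds with a slight attributed fall would enter the event count of all of these. Enrollment began in June 2024 and the last follow-up visit is expected in June 2029, so events are being classified while the definition stands in this form.

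**Working it through.** **Inputs from the article**
- Threshold as written: a fall of at least 2 mg/dL (Outcomes).
- Minor bleeding: every bleed that meets no major criterion (Outcomes).
- Patients needed for model development: largest for SSE, at 3,334, and 3,667 in total with 10% loss (Sample size calculation).

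**Inputs assumed, because the article does not give them**
- Laboratory reporting step for hemoglobin: 0.01 to 0.1 g/dL.
- Hemoglobin levels for illustration: 8 to 16 g/dL.

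**1. Unit conversion.** 1 g = 1,000 mg, so 2 mg/dL = 2 / 1,000 = 0.002 g/dL. Against the same figure in g/dL: 0.002 / 2 = 0.001, one thousandth.

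**2. Comparison with the smallest recordable fall.**

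| Reporting step (assumed) | In mg/dL | Multiple of the written threshold |
|---|---|---|
| 0.1 g/dL | 100 | 100 / 2 = 50 |
| 0.01 g/dL | 10 | 10 / 2 = 5 |

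The smallest fall that can be recorded exceeds the threshold at both ends of the range, so the conclusion does not depend on the step chosen.

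**3. Relative size of the fall.**

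| Hemoglobin (assumed) | Fall of 2 mg/dL | Fall of 2 g/dL |
|---|---|---|
| 8 g/dL | 0.002 / 8 = 0.025% | 2 / 8 = 25% |
| 16 g/dL | 0.002 / 16 = 0.0125% | 2 / 16 = 12.5% |

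**4. Effect on the article's own classification.** By step 2, any bleed to which a recordable fall is attributed meets the written criterion, including one from a site such as the nose or skin. Minor bleeding then keeps only bleeds outside the listed critical sites for which no fall was measured or attributed. A two-level severity scale cut at that point no longer grades severity.

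**5. Search for a correction elsewhere.** Table 4, the adjudication sentences, Data management, Statistical analysis and Study strengths were compared with the definition. None states a hemoglobin threshold, and none says that the cited criteria override the wording given.

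**6. Sample size.** The plan's own figure reproduces: 3,334 x 1.10 = 3,667.4, printed as 3,667. The article says that "the number of patients needed for predictive model development was highest at 3,334 for SSE". Bleeding is therefore not the binding outcome, and the bleeding threshold does not enter the printed number.

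**The case against.** The strongest reply is that this is an evident slip of the pen. The same bullet names and cites published criteria, and clinicians are unlikely to apply a cut-off that no laboratory can resolve. Source documents for all outcomes go to a central adjudication committee, with central data review, queries and monitoring at every site. What is at hand is a journal article, and the operational documents may carry the right unit.

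Much of this stands. The slip is probably typographical, and central adjudication makes it less likely that final classification follows each site's reading of the unit. It does not cure the text. After naming the criteria the article spells out its own definition, and the adjudicators are given no other written threshold. Nor is this a detail left to a fuller document: the threshold is stated, and stated wrongly.

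A reader might go further in three directions that the article does not support.
- *A misclassification rate.* One could work out how often two hemoglobin values differ by chance and call that the share of trivial bleeds promoted to major. But the criterion requires bleeding that leads to the fall, and nothing says that trivial bleeds have paired measurements.
- *Loss of comparability with Phase 1.* The Phase 1 bleeding definition is not given, so this cannot be asserted.
- *Systematic differences between sites.* Central adjudication limits these, and no text shows that sites classify on their own.

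**Conclusion.** The point holds as an error of unit in the operative definition of a primary-objective and prediction-model outcome. The written threshold is smaller by a factor of 1,000 than the same figure in g/dL, and smaller by a factor of 5 to 50 than the smallest recordable fall under the assumed reporting steps. Taken literally, it nearly removes the distinction between major and minor bleeding.

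The factor of 1,000 is pure unit arithmetic. The factor of 5 to 50 rests on the assumed reporting step. That g/dL was intended is an inference: the written unit is unworkable, and the cited criteria are not reproduced in the article. How many bleeds, if any, have been classified under the written unit cannot be told from it. Despite being a probable typing error, this deserves correction before bleeding events are analyzed, because it is the only numeric criterion for the outcome. The planned 3,667 patients are not affected.

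**What to change.** 1. In the Outcomes definition, change the unit of the hemoglobin fall from mg/dL to g/dL, after confirming figure and unit against the criteria cited there.
2. Check whether the web-based system and the instructions used by the adjudication committee carry the same unit. Neither is shown, so the error should not be presumed there.
3. Only if they do, correct them and have the committee re-check the bleeds classified under the written unit.

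Step 1 costs one unit in one sentence. Step 2 is a brief check. Step 3 arises only if the error has spread, and its cost depends on the number of bleeds recorded by then, which the article does not give. No change to sample size, schedule or analysis methods follows.
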